### Blinding of interventions

To the extent possible, the interventions have been blinded. All teams/players were told that they are involved in an assessment of the value of their training programme. No team was told to which arm of the trial they had actually been allocated nor were they specifically told that the outcome of interest is knee injury prevention. All players are required to adopt their allocated exercise training programme throughout the playing season.

As the study is being conducted in two states, the study teams are being drawn from a large base and therefore we do not expect contamination of the study arms. The club-based PDCs are unaware of the study design as a two-arm RCT and thus operate independently believing that the study is investigating the relationship between their training programme and injury profile. Thus, the monitoring of injuries and player exposure is independent of, or blinded to, the other interventions.

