### Primary data collectors

All field work procedures are rigidly standardised and based on methods previously developed, piloted and used in similar Australian football studies.^11^ ^35^ ^36^ ^38^ ^41^ The good to high reliability and validity of these data collection methods has already been demonstrated.^36^ ^38^ The day-to-day conduct of the RCT is being coordinated by a project manager in each state.

The appointed project managers train and coordinate the activities of a nominated person within each team (ie, the primary data collector or PDC), who is responsible for data collection on site. The PDC is also the team’s exercise trainer for training sessions and game, which has been a major incentive to attract teams into the study and ensure compliance. It is their role to ensure that the RCT training intervention is run in cooperation with the team coaches, and to ensure that players are compliant and progress to more advanced training tasks as they become more proficient.

It was compulsory for all PDCs to attend a separate formal training session for the intervention arm that covers all study procedures. A detailed procedures manual was disseminated to all PDCs and the clubs they are associated with; these contain the standardised data collection forms for recording exposure, compliance and injuries as well as full details of the coding and classification schemes. During the training sessions, practice exercises on specific examples were undertaken to address any discrepancies before the data collection period starts.

Previous research has demonstrated the use of PDCs in this context as a valid and reliable means of exposure, compliance and injury data collection.^36^ ^38^ ^41^ Club-based PDCs have the particular advantage of knowing all members of the team well and being able to determine very quickly and accurately if a player is missing from a game or training session and determining the reasons why (eg, related to injury?). The accuracy of the PDC activities is being assessed through double counting of exposure and injury data at randomly selected games.^38^ The work being undertaken by the PDCs is not very different from standard practice in Australian Football clubs, which already typically involves the recording of the team members present and any injuries that occur.

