### Injury and exposure details

The PDCs record the occurrence of all injuries and their circumstances, and provide injured player details for each game and training session using previously used standardised methods.^12^ ^35^ ^41^ A standardised form is used to provide a simple description of injury and notification that the player was seen by a doctor or sent to hospital. This information is obtained from the PDCs each week.

A self-report injury diagnosis will be obtained from the player after they have sought medical or other treatment for that injury. The injured player will also be asked to provide the details of the person who provided their treatment, so that their self-report information can be validated and full details of the diagnosis obtained from their medical practitioner. Medical records pertaining to injuries sustained during the games will also be obtained, and the injury descriptions reviewed by an associate investigator with medical qualifications. A medical diagnosis will be obtained and coded for each case, and this will be checked with the original notification of injury.

For each player, the amount of time spent playing Australian Football (both competition and training) over each week of the trial is recorded by the PDC. This is done in accordance with the methods previously developed for other community-based Australian Football injury studies.^12^ ^35^ ^41^ ^43^ Exposure is recorded during each training session and game.

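### Injury and exposure monitoring is called independent of, or blinded to, the interventions, but the person recording them is the team's exercise trainer and helps run the programme

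*Protocol article*

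**What the plan says.** Under Blinding of interventions, the article says the interventions were blinded as far as possible. On the data collectors it states: "The club-based PDCs are unaware of the study design as a two-arm RCT". It adds that they work independently, "believing that the study is investigating the relationship between their training programme and injury profile", and concludes: "Thus, the monitoring of injuries and player exposure is independent of, or blinded to, the other interventions".

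Under Primary data collectors, the same people have a second role: "The PDC is also the team’s exercise trainer for training sessions and game". Further, "It is their role to ensure that the RCT training intervention is run in cooperation with the team coaches", and they must see that players comply and move on to harder tasks. On training: "It was compulsory for all PDCs to attend a separate formal training session for the intervention arm that covers all study procedures".

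Under Injury and exposure details, the PDC records every injury and each player's weekly playing and training time. Under Compliance, the PDC also records whether players complied. The PDC therefore supplies the numerator and the denominator of the injury rate, as well as the compliance index.

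**The concern.** Not knowing that a comparison arm exists is different from being blind to the programme one is running. The claim of independence rests on the first, whereas the quality of injury recording depends on the second. A PDC who trains the team and knows that injury under that programme is being studied may record injuries or hours differently from a PDC running the control programme.

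The content of the two programmes also differs in what it signals. The intervention exercises are directed at the muscles around the knee. The control teams' extra exercises were chosen to be biomechanically distinct.

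The outcome at stake is the knee injury rate. The article labels no outcome primary, but the knee ligament injury rate is the first hypothesis and the knee injury rate is the basis of the sample size.

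**Working it through.** **1. The statements side by side**

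| Question | What the article says | Section |
|---|---|---|
| What is the PDC unaware of? | The two-arm design | Blinding of interventions |
| What does the PDC believe is studied? | The link between the team's own programme and injury | Blinding of interventions |
| Who trains the team and sees that the programme is run and progressed? | The PDC, with the coaches | Primary data collectors |
| Who records injuries and exposure? | The PDC | Injury and exposure details |
| Who records compliance? | The PDC | Compliance |

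The first two rows support unawareness of the other arm. The last three rule out independence from the PDC's own programme.

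**2. The training sentence**

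If every PDC attended a session described as being for the intervention arm, control PDCs had reason to suspect a second arm. If only intervention PDCs attended, training in data collection may have differed by arm. Neither reading fits easily with the blinding section.

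**3. What the safeguards reach**

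- Self-report after treatment, contact with the treating practitioner, medical records and review by a medically qualified associate investigator limit mislabelling of an injury once it is notified. The coded diagnosis is checked against the original notification, so this route mainly verifies notified cases.
- Double counting can detect injuries never notified and hours wrongly recorded, but only at the randomly selected games.
- The sham programme and the undisclosed knee outcome make differing expectations less likely. They do not make the recorder independent of the programme.

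**4. Illustration of scale**

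Inputs from Sample size: control rate l0 = 0.020 per game-hour, rate ratio 0.65 (l1 = 0.013), y = 600 game-hours per team, between-team coefficient of variation k = 0.35, power 80%. Two-sided alpha of 0.05 is assumed.

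The plan's own figure first:

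teams per arm = (1.96 + 0.842)² × [(l0 + l1)/y + k²(l0² + l1²)] / (l0 − l1)²

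- With k = 0: 8.81 (the article gives 8.8).
- With k = 0.35: 19.97 (the article gives 20).
- Ratio: 19.97/8.81 = 2.27, as stated.

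The sample size reproduces, and nothing in this point disputes it.

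The documents give no figure for differential recording, so the proportions below are assumed. With 20 teams per arm, the apparent rate ratio is the true ratio times s, where s is intervention-arm recording relative to control. The standard error is √{[(l0 + l1)/y + k²(l0² + l1²)]/20}, where l1 is now l0 times the apparent ratio.

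| True ratio | s | Apparent ratio | Chance of a significant result favouring the intervention |
|---|---|---|---|
| 1 | 1.00 | 1.00 | 2.5% |
| 1 | 0.95 | 0.95 | 5% |
| 1 | 0.90 | 0.90 | 11% |
| 1 | 0.80 | 0.80 | 33% |
| 0.65 | 1.00 | 0.65 | 80% |
| 0.65 | 1.10 | 0.715 | 61% |
| 0.65 | 1.20 | 0.78 | 39% |

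The first four rows assume no true effect and equal or under-recording in the intervention arm. The last three assume the targeted effect and equal or over-recording there. The apparent ratios simply restate the assumption. What the table adds is that modest differences in recording would matter in a trial of this size.

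**The case against.** The strongest reply is that the blinding section is qualified and speaks of the other interventions. It tells readers that PDCs know their own programme and claims only that they do not know of the comparison. That is a fair reading of part of the sentence, but it does not rescue the word independent, because the PDC helps to run the programme.

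The dual role is also a deliberate choice for a community trial. The article gives its reasons: it attracts teams, supports compliance, and uses someone who knows the players. These are good reasons to keep the role, but they do not support the blinding claim.

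The safeguards carry real weight. Control teams receive a sham programme, and the exercise-trainer role is not limited to one arm, so control PDCs may be just as committed to their own programme. Teams were not told that knees were the target, and all injuries are recorded whatever their site.

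A reader might infer three stronger points that the documents do not support:

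- **That any bias favours the intervention.** A PDC with more training could equally record injuries more fully, which would work against it.
- **That 10–20% of injuries go unrecorded.** This is an assumption used to show scale.
- **That the medical reviewer knows the arm.** A condensed article does not mention masking of the reviewer, and that silence is not evidence of its absence.

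**Conclusion.** The contradiction stands. The article claims independence or blinding of injury and exposure monitoring, and its own description of the PDC's duties does not allow it. What can be claimed is that PDCs are unaware of the two-arm comparison, and even that must be reconciled with the sentence on training for the intervention arm.

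Recording could therefore differ by arm. Neither the direction nor the size can be determined from the documents, and no figure in the article changes. The planned safeguards reduce the risk. What remains lies mainly in injuries never notified, which double counting reaches only at sampled games. The trial remains viable, but the statement should be corrected because readers will rely on it when judging the knee injury result.

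**What to change.** 1. Restate the conclusion of the blinding section: PDCs are unaware of the two-arm comparison, but are neither blind to nor independent of their own team's programme.
2. Reconcile the sentence on the PDC training session with that statement, saying who attended which session and what it revealed about the arms.
3. If this is not already done, remove team and arm from the records given to the existing associate investigator, and use that coded medical diagnosis to classify knee ligament injuries.
4. Report agreement between the PDC and the second count, for injuries and for exposure, separately by arm, using the double-counted games already planned.
5. Add a sensitivity analysis restricted to practitioner-treated injuries, where the PDC has less discretion. It will not recover treated injuries that were never notified, so it complements step 4.

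The cost is a few sentences, some redaction and a little extra analysis, with no new staff or fieldwork. The small downside is that untreated mild injuries do not count in the sensitivity analysis.

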### Adjustment for, and strategies to overcome, potential confounding

A possible confounder of the relationship between the training programmes and injury outcomes are the ground conditions, particularly as the RCT is to be conducted in two different states. Research on injury in elite Australian Football players has identified ground conditions as an important factor,^54^ but this has not been explored in community-level players. Using previously published methods, a ground conditions report is obtained for all matches. This includes assessment of (*a*) soil and grass type (obtained from the groundsperson and classified as mainly couch grass, mainly rye, etc and natural sand base, sandy loam, etc) and (*b*) rainfall reading on the day of the game (obtained from a nearby weather station). If the Australian Football grounds are close to where rainfall is recorded by the Bureau of Meteorology, then it is easy to collect daily rainfall data for up to a year before.

Information on additional exercise undertaken by players is collected directly from players at both preseason and end-of-season surveys. This includes information on the type, frequency and intensity of such exercise and will be adjusted for in the analysis. Any additional exposure is expected to be evenly distributed across the two arms; therefore there is very little risk of non-differential misclassification of exposure.

### Behaviour, attitudes and knowledge

In addition to the RCT, the attitudes, knowledge and behaviours of the players with regard to the interventions are being determined both before and after the interventions are implemented. This has been undertaken through surveys of all players involved in the RCT both preseason and postseason using a standard questionnaire, based on those developed previously^39^ ^44^ ^45^ ^47^ ^49^ and including measures of risk, playing and injury history and basic sociodemographic profile. The surveys assess, in particular, whether players in different study arms hold different risk perceptions and modify their behaviours accordingly, and whether these change over the seasons.

### Compliance

This study has been optimally designed to maximise compliance in a community sport setting. However, this aspect is being monitored vigilantly throughout the study and any contamination in the control arm will be adjusted for in the final analysis.

The coach of an Australian Football team, in conjunction with the referee, has jurisdiction over the behaviour of his/her team’s members and plays a very important role in this by ensuring that players comply with the interventions. This is standard Australian Football practice and will be used to the projects’ full advantage.

The PDCs record whether or not players are compliant during each trial week on a data record sheet. These data will be combined over all exposure episodes, and an index of compliance (such as percentage of exposure episodes that were compliant) will be computed for each player. Experience from previous work^37^ ^51^ ^55^ has shown that coaches do support injury prevention research and are particularly supportive of interventions such as those proposed here, which could also enhance their team’s performance.

The project is being conducted at the upper levels of community Australian Football—that is, division 1 and A grade amateur players. As players and coaches from these levels are more motivated to play well, and therefore more likely to be motivated to undertake training programmes, that could help this.

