### Analysis

At the start of the RCT, retrospective injury data are obtained to determine equivalence in injury risk at baseline. Injury, exposure and compliance data are being collected during each month of the Australian Football season, and the outcome measures of interest are the total numbers of injuries, total exposure and overall compliance rates over the entire study period. All data will be pre-coded and double-entered into a PC database.

All analyses will be undertaken with the Stata analysis package and performed on an intention-to-treat basis with the control arm (arm 1) as the reference group. The analysis of biomechanical outcomes will take clustering of individuals within teams into account through the use of generalised estimating equations. Poisson or negative binomial regression, as appropriate, will be used to analyse injury rates with estimation of a scale parameter allowing for cluster effects.

Behavioural, attitudinal and knowledge variables will be assessed by a number of different items on a questionnaire. Responses will be scored, and the scores from different items combined to give an overall attitude score on a quasi-continuous scale. Scores will be compared preseason to postseason, and changes compared across study arms. The attitudes and behaviours of players, particularly attitudes before and after, will be compared by categorical data analysis again using generalised estimating equations to allow for cluster effects. Information about injury outcomes (ie, time away from sport and amount of treatment received) will be collected from all injured players so that the cost per injury can be calculated.

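### Intention-to-treat is promised beside unlabelled adjustments for control-arm contamination and end-of-season exercise, which arise after randomisation and could bias the rate ratio either way

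*Protocol article*

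**What the plan says.** Three commitments in the protocol article bear on the point.

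- **Analysis:** all analyses are to be "performed on an intention-to-treat basis with the control arm (arm 1) as the reference group". The injury model follows: "Poisson or negative binomial regression, as appropriate, will be used to analyse injury rates with estimation of a scale parameter allowing for cluster effects".
- **Compliance:** "any contamination in the control arm will be adjusted for in the final analysis". The data come from weekly records kept during the season by the primary data collectors (PDCs): "The PDCs record whether or not players are compliant during each trial week on a data record sheet".
- **Adjustment for, and strategies to overcome, potential confounding:** "Information on additional exercise undertaken by players is collected directly from players at both preseason and end-of-season surveys". The article says that this covers the "type, frequency and intensity of such exercise and will be adjusted for in the analysis". It gives as reassurance that "Any additional exposure is expected to be evenly distributed across the two arms".

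No section calls either adjustment secondary, supplementary or a sensitivity analysis. No section says which of the two exercise measurements enters the model. The method of adjusting for contamination is not stated.

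**The concern.** An ITT comparison is protected by randomisation because the arms differ only by allocation and chance. That protection does not extend to a model that conditions on something that happens after allocation and may be changed by it, or by the outcome.

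Contamination can occur only among controls and only once the season is under way. Teams or players who pick up preventive exercises may differ in underlying injury risk from those who do not. End-of-season exercise may respond to the allocated programme, and an injury may change how much a player exercises afterwards.

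At stake is the main answer of the trial. An analyst who follows these sentences literally, with ordinary covariates, would report a rate ratio that is not the effect of allocation. For a trial whose stated objective is effectiveness in real-world community football, the effect of allocation is the natural quantity to report.

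**Working it through.** **Timing.** The Project time frame places randomisation in January to March, attitudinal surveys in March to April and the intervention in March to August of each season. Contamination and end-of-season exercise can therefore only be observed after randomisation. The preseason survey is close to baseline but may fall after randomisation.

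**Can allocation affect these variables?** The exercise adjustment is defended by expecting balance across arms. The section on behaviour, attitudes and knowledge nevertheless sets out to learn "whether players in different study arms hold different risk perceptions and modify their behaviours accordingly, and whether these change over the seasons". The article thus treats a difference in behaviour by arm as an open question.

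**Inputs from the Sample size section.** Control rate 20 per 1000 game-hours, rate ratio 0.65 (rates λ0 = 0.020 and λ1 = 0.013), y = 18 × 20 × 100/60 = 600 game-hours per team, team coefficient of variation k = 0.35. A two-sided 5% level is assumed, since none is stated.

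**The plan's own figure.** With (1.960 + 0.842)² = 7.849:

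- Without clustering: 7.849 × (0.033/600)/0.007² = 8.81 teams.
- Multiplier: [0.033/600 + 0.35² × (0.020² + 0.013²)]/(0.033/600) = 2.267.
- Product: 19.97, which agrees with the stated 8.8, 2.27 and 20 teams per arm.

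The sample size is not in dispute. These values anchor the illustrations below.

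**Contamination as a covariate.** A binary contamination indicator exists only among controls, so a model containing arm and that indicator compares all intervention units with uncontaminated controls. That subset is not randomised. The effect was illustrated by large-sample Poisson simulation (400,000 units). The assumptions were a full-uptake rate ratio of 0.65, about 20% to 24% of control units contaminated at full effect, and an unmeasured risk factor with log-rate coefficient 0.35 per SD. That coefficient implies a coefficient of variation of √(exp(0.35²) − 1) = 0.36, close to the plan's.

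| Log-odds link, risk factor to contamination | ITT ratio | Adjusted ratio |
|---|---|---|
| −1 (low-risk units adopt) | 0.696 | 0.611 |
| −0.5 | 0.693 | 0.627 |
| 0 | 0.699 | 0.651 |
| +0.5 | 0.710 | 0.676 |
| +1 (high-risk units adopt) | 0.726 | 0.704 |

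The adjusted ratio is never the ITT ratio. It recovers the full-uptake value of 0.65 only when contamination is unrelated to risk, and it errs in both directions otherwise.

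**End-of-season exercise as a covariate.** Let exercise = a × arm + 0.5 × risk factor + unit-variance noise, with no effect of its own on injury. The fitted exercise coefficient is then 0.35 × 0.5/(0.5² + 1) = 0.14, and the log rate ratio for arm shifts by −0.14a.

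- a = −0.5: 0.65 × exp(0.07) = 0.697 (simulated 0.698).
- a = +0.5: 0.65 × exp(−0.07) = 0.606 (simulated 0.606).
- No arm shift, or no shared cause: 0.65, unchanged.

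These runs leave out any effect of injury on later exercise and any effect of exercise on injury. Either would add a further reason not to condition on the end-of-season value.

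**The case against.** The strongest defence is that the text does not state a wrong analysis. It states an adjustment without a method, and a sound method (allocation as instrument) would satisfy the same sentence. A condensed article may leave that choice to the full protocol or SAP. The plan also guards against contamination through two states, teams not told their arm and PDCs unaware of the two-arm design, and it says that none is expected. There is a real motive to adjust as well. If 10%, 20% or 30% of control exposure were contaminated at full effect, the ITT ratio would be 0.013/[0.020 × (1 − 0.35c)] = 0.674, 0.699 or 0.726, and power with 20 teams per arm about 73%, 64% or 55%.

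Much of this stands. The method is open, contamination may prove rare, and a contamination analysis is worth having. What remains is that the article commits to both adjustments without a label or a limit. That is a stated rule and not mere silence.

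Several stronger readings are tempting but unsupported:

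- *The sections prescribe two different primary results.* No primary analysis is named. The word final may refer to timing, since the Project time frame separates preliminary analysis after each season from data analysis in 2009.
- *ITT is broken outright.* Nothing moves, excludes or reclassifies a team, so analysis by allocated arm is kept. What is at risk is the ITT effect estimate.
- *Injured or non-responding players are dropped.* Nothing specifies a complete-case analysis.
- *Every post-randomisation variable must be barred.* Match-day ground conditions and rainfall are recorded after randomisation, but an exercise programme cannot change them.

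**Conclusion.** The point holds as an unlabelled and unrestricted commitment to adjust for variables that arise after randomisation, set beside an ITT promise that covers all analyses. If contamination or end-of-season exercise enters as an ordinary covariate, the rate ratio no longer estimates the ITT effect and can be biased in either direction.

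The size is unknown. The documents give no contamination rate and nothing on how contamination or exercise relates to risk. Under the assumed values above, contamination-adjusted ratios ran from 0.61 to 0.70 against ITT ratios of 0.69 to 0.73, and exercise adjustment moved 0.65 to 0.61 or 0.70. These figures show that the choice could matter; they do not predict a bias in this trial. In the exercise setting simulated, the bias disappears if allocation does not shift exercise or if exercise and injury share no cause. The preseason exercise value is not part of the objection, provided that it is taken before the programme starts.

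**What to change.** Amend the Compliance, confounding and Analysis sections as follows, before outcome data are analysed.

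1. State that the primary result is the injury rate ratio by allocated arm, adjusted only for variables that allocation cannot affect. These are baseline or preseason measures taken before the programme starts, state, ground conditions and rainfall.
2. Limit the exercise covariate to the preseason value. Keep end-of-season exercise out of that model and report it descriptively by arm.
3. Move contamination and compliance to a labelled secondary analysis with a method that preserves randomisation, such as a complier-average effect with allocation as instrument, reported beside the primary result.

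The cost is a few sentences and one additional secondary analysis. No new data are needed and the sample size is unchanged. The primary result will stay diluted by any contamination that occurs, as an ITT effect should, and the secondary analysis addresses the effect of uptake.
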